#### The neurocognitive training

The neurocognitive remediation will be done by using the Neuropsychological Educational Approach to Cognitive Remediation (NEAR) [46,47]. NEAR is an evidence-based approach that focuses on aspects such as learning and motivation when doing CR. The patients will receive individual neurocognitive training on a computer followed by a group discussion that aims at relating the cognitive exercises to real-world activities. In addition to the group training the patients are instructed to do at least 1 h per week of computerised training at home.

#### The social cognitive training

The overall aim of the social cognitive training is to enhance the skills that enable the patients to understand the thoughts and intentions of others and to respond adequately in social situations. The social cognitive training will be by use of the Social Cognition and Interaction Training (SCIT) manual developed by Roberts et al. [48], which takes the form of group psychotherapy and skills training. It addresses several of the key social cognitive domains, comprising intolerance of ambiguity, attributional biases in explaining negative events, theory of mind (ToM), and emotion perception abnormalities*.* It is the assumption that these social cognitive skills hinder adequate social behaviour in schizophrenia and psychosis-like states.

#### Individual sessions

The individual sessions serve the purpose of maximising the transfer of the effect of the group training to the daily lives of the patients. The individual sessions are embedded in cognitive behavioural therapy (CBT) and use core CBT techniques such as goal setting, modifying distorted thinking, problem solving, and role-play. The content of the individual sessions will be tailored to fit the specific problems of the patient. The sessions will follow a manual that frames the sessions. However, it must be taken into account that the sessions cannot be completely manualised as the therapist approach and CBT techniques used will depend on the individual problem.

### Fidelity to treatment manual

The intervention is manual-based, which improves standardisation of the treatment. [name], co-author of the SCIT manual [48], has given a training course at the Mental Health Centre Copenhagen to ensure a proper understanding and use of the SCIT manual as well as adherence to it. The therapists will be offered bi-weekly Skype supervision from [name] throughout the trial.

A selected number of group sessions will be videotaped and used to rate adherence to the treatment manual by independent raters. The adherence will be rated by use of the SCIT Fidelity Scale (appendix in the SCIT manual) [48].

### Standard intervention in the experimental group

The standard intervention in the experimental group is planned to be similar to the standard intervention in the control group (see description below).

### Standard interventions in the control group

Patients allocated to the control group are free to choose whatever standard treatment they are offered by the clinicians managing their treatment. Usually standard treatment consists of a somewhat regular contact to health professionals in the in- and outpatient facilities in the capital region of Denmark (e.g., community psychiatric centres or private specialists in psychiatry). It involves monitoring of psychopharmacological treatment and different kinds of supportive counselling, e.g., concerning their psychiatric symptoms, relating to functional domains, or a more regular psychotherapeutic intervention depending on the nature of the health-service managing their treatment. In contrast to the intervention group, standard treatment does not involve specific cognitive training.

The standard treatment provided to both the experimental and control group will be carefully registered in retrospect at the end of the trial by an independent blinded assessor using a checklist comprising items such as use of medication, psychological interventions, number of sessions, and therapist skills.

#### Medications

Patients in both treatment groups are allowed to receive medication. In case an antipsychotic-naïve patient develops psychosis during the trial, this will be reported to the health service managing the treatment in order for them to initiate antipsychotic treatment.

### Assessments

Assessments will be conducted at baseline, prior to randomisation, as information from the baseline assessment is used to perform stratified randomisation and validate inclusion and exclusion criteria. The assessments will be performed at cessation of treatment 6 months after randomisation and at follow-up 12 months after randomisation.

#### Diagnosis

The Comprehensive Assessment of At-Risk Mental States (CAARMS) [45] is used to classify patients as being at UHR for psychosis as well as assessing for transition to psychosis during the trial period. The Structured Clinical Interview for DSM-IV (SCID) [49,50] will be used to assess diagnosis.

The CAARMS is a validated instrument showing good to excellent reliability [45].

#### Neurocognitive function

Neurocognitive function will be assessed using a comprehensive test battery including the Danish Adult Reading Test (DART), a Danish adaptation of the National Adult Reading Test [51]; four subtests from the Wechsler Adult Intelligence Scale-Third Edition (WAIS-III) [51]; Vocabulary, Similarities, Block Design and Matrix Reasoning; the Brief Assessment of Cognition in Schizophrenia (BACS) battery [52]; and the Behavior Rating Inventory of Executive Functions-Adult Version (BRIEF-A) [53]. Furthermore, patients will undergo the following computerised tests from the Cambridge Neuropsychological Test Automated Battery (CANTAB) [51]: Motor Screening Test, Spatial Span, Spatial Working Memory, Emotion Recognition Task, Stockings of Cambridge, IED Set Shifting Test, Paired Associate Learning, 5-Choice Serial Reaction Time, and Rapid Visual Information Processing.

The BACS is specifically designed to detect cognitive changes in response to treatment. The validity and reliability properties of the BACS have been established in patients with schizophrenia and healthy controls, and the BACS composite score has proven high test-retest reliability, increasing the likelihood of detecting a treatment-related effect [52,54,55].

The tests included in the CANTAB battery have proven high validity [56,57]. The reliability of the CANTAB tests varies between individual tests. High reliability (*r* > 0.8) has been shown on measures of visual processing, e.g., the Paired Associates Learning task, while lower reliability has been found particularly on measures of executive functions, e.g., sub-measures of the IED Set Shifting Task [58]. This lower reliability of tests that assess executive functions is very difficult to avoid because of the necessary task novelty involved in assessing executive processing [58].

#### Social cognitive function

Social cognitive function will be measured with The Awareness of Social Inference Test (TASIT) [59], the High-Risk Social Challenge task (HiSoC) [60], the Social Cognition Screening Questionnaire (SCSQ) [61], and Social Responsiveness Scale (SRS) [62].

#### Symptomatology

General symptomatology, negative, depressive, and manic symptomatology will be measured with the Brief Psychiatric Rating Scale Expanded Version (BPRS-E) [63], the Scale for the Assessment of Negative Symptoms (SANS) [64,65], the Montgomery-Åsberg Depression Rating Scale (MADRS) [66], the Young Mania Rating Scale (YMRS) [67], and the Clinical Global Impression (CGI) [68]. Nine cognitive-perceptive basic symptoms from the Schizophrenia Prediction/Proneness Instrument-Adult Version (SPI-A) [69] will be used as a measure of subjectively experienced cognitive-perceptive symptoms.

#### Psychosocial function

Three measures will be included to assess psychosocial functioning: the Personal and Social Performance Scale (PSP) [70], Social and Occupational Functioning Assessment Scale (SOFAS) [71], and Global Functioning: Social and Role Scales [72].

### Adverse events

The participants’ well-being will be a primary focus during the trial. Accordingly, their safety will be monitored and accurately reported throughout the treatment period. CR is not known or expected to cause adverse events [77]; therefore, we do not expect any adverse events to occur. However, should an adverse event occur, it will be dealt with properly by the therapists in charge of the treatment. Using our outcome instruments we will investigate whether the FOCUS intervention causes nominally worse scores, which will be interpreted as a possible indication of harm.

### Setting of assessment

All the assessments will take place at the Mental Health Centre Copenhagen. Most tests are assessed using paper and pencil with the exception of CANTAB, which is a computerised test battery, and the HiSoC test, which uses videotaping. The staff members performing the SCID interview are psychologists and medical doctors who have undergone a 4-day training course using the SCID diagnostic interview co-supervised by [name].

### Data management

All the data will be stored in locked cabinets at the Mental Health Centre Copenhagen in pseudo-anonymised form (i.e., identifiable only with project codes, which are stored separately from the project key identifying the codes). The data will be completely anonymised after publication of all results. The participants’ privacy will be protected by the Danish Data Protection Agency, which has approved the trial.

Databases will be kept locally at the Mental Health Centre Copenhagen under blinded conditions (see Blinding).

### Outcomes and sample size calculation

#### Primary outcome

The primary outcome is overall cognitive function, measured with the BACS composite score 6 months after randomisation.

### Sample size calculation

The sample size calculation is based on our primary outcome, a priori defined to be the between-group difference at 6 months on the BACS composite score. We consider a clinically relevant difference on this scale to correspond to a Cohen’s *d* of 0.50 (e.g., assuming a between-group difference of 3.0 and a pooled SD of 6.0) [29]. With a two-sided alpha of 0.05 and power of 80%, this will require 63 participants to be randomised to each of the two interventions.

### Secondary outcomes and power calculations

The difference in global personal and social functioning 6 months after inclusion will be measured with the PSP. With 63 participants in each group, and assuming a pooled standard deviation of 10 points [72,78-81], we will have more than 97% power to detect a difference of 7 points between the groups, which would be considered the minimal clinically relevant difference on this scale [82].

The BPRS-E will be used to measure symptomatology (e.g., psychosis-like symptoms). The BPRS scale is expected to have a pooled standard deviation of 20.0 points [83]. Given a sample size of 63 per group and a two-sided alpha of 0.05, we have 80% power to detect a difference between the two groups of at least 10.06 points. Antipsychotic treatment and psychotherapeutic interventions have been shown to reduce BPRS by more than 12 points [5,84], indicating that we have sufficient power to detect the minimally relevant difference on this secondary outcome.

Negative symptomatology will be assessed using the SANS. The SANS scale is expected to have a pooled standard deviation of 13 points [5]. Given a sample size of 63 per group and a two-sided alpha of 0.05, we have 80% power to detect a difference between the two groups of at least 6.54 points. Treatments with cognitive and supportive therapy as well as risperidone have been shown to reduce SANS by more than 7 points [5]. This indicates that we have sufficient power to detect the minimally relevant difference of this secondary outcome.

Depressive symptoms will be assessed using the MADRS. Data from a previous randomised clinical trial with UHR patients shows a SD of 9.56 points [6]. Allowing for larger variance in data we set a SD of 10 when calculating detectable differences. With our sample size of 63 per group and a two-sided alpha of 0.05, we have 80% power to detect a difference between the two groups of at least 5.03 points.

### Exploratory outcomes

Exploratory outcomes will be transition to psychosis assessed by the CAARMS; symptomatology assessed by the CAARMS and SPI-A; and social cognition assessed by the ERT, TASIT, HiSoC, SCSQ, and SRS. Psychosocial function will be measured with the SOFAS and Global Functioning: Social and Role Scales. Additionally, the BRIEF-A will be used as a proxy measure of daily functioning. Patients perceived quality of life will be assessed with the QOLS, and lastly the number of participants experiencing adverse events will be recorded.

### Randomisation

Randomisation will be centralised with a concealed randomisation sequence carried out by the Copenhagen Trial Unit (CTU). Randomisation will be stratified by current use of antipsychotic medication (yes/no) and the IQ score (≤100/>100). Block size will be unknown to the investigators and clinicians.

Signed informed consent will be obtained prior to randomisation. The randomisation is computerised and central. The blinded assessors will enter the participant’s data on a webpage hosted by the CTU. Thereafter, a computerised randomisation is performed, and an email is sent to an independent member at Mental Health Centre Copenhagen revealing to which intervention programme the participant has been allocated. The staff member then contacts the participant and informs him or her of the result of the randomisation. The randomised intervention allocation is concealed until the statistical analyses of resulting data have been completed.

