## Methods

### Recruitment

The FOCUS trial is a randomised, blinded, parallel-group superiority clinical trial, enrolling a total of 126 help-seeking patients from in- and outpatient facilities in the catchment area of Copenhagen (Figure 1). Patients meeting standardised ‘at-risk’ criteria based on the Comprehensive Assessment of At-Risk Mental States (CAARMS) [45] will be approached about participating in this clinical trial. Patients will be randomised (1:1) to intensive CR plus standard treatment versus standard treatment, as described in further detail in the section Interventions.

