### Statistical analyses

The planned comparisons between the two groups on continuous outcomes will be carried out with a generalised linear model adjusted for stratification variables, potential baseline imbalances, and skewed attrition, with missing data handled by multiple imputations. As an important secondary assessment of this type of outcome, linear mixed model analyses with repeated measurements and an unstructured covariance matrix will assess the interaction term between time and intervention. For non-normally distributed continuous outcome measures, non-parametric analyses will be applied. For dichotomous outcomes, logistic regression will be applied, and for time to transition, Cox proportional hazards regression will be applied. All analyses will be according to the intention-to-treat principle, analysing all participants in the groups they were assigned to by randomisation. We expect to encounter missing data, and this will be handled with the linear mixed models and multiple imputations as appropriate. A blinded and independent statistician who has no contact to the trial participants will conduct the primary efficacy analyses.

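### The primary model assures adjustment only for the stratification variables; baseline BACS, probably the best predictor of the outcome, enters only if it counts as a baseline imbalance

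*Protocol article*

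**What the plan says.** All references are to the protocol article; the SAP is not shown.

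- *Primary outcome*: overall cognitive function, "measured with the BACS composite score 6 months after randomisation".
- *Randomisation*: stratified by current antipsychotic use (yes/no) and "the IQ score (≤100/>100").
- *Statistical analyses*: continuous outcomes are compared with a generalised linear model "adjusted for stratification variables, potential baseline imbalances, and skewed attrition", with multiple imputation for missing data. A repeated-measures mixed model is planned as an important secondary assessment. Missing data are expected.
- *Assessments*: the baseline assessment precedes randomisation and supplies the information for the strata. *Neurocognitive function* lists the BACS, the DART and "four subtests from the Wechsler Adult Intelligence Scale-Third Edition (WAIS-III"). The article does not say which test yields the IQ score.
- *Sample size calculation*: "assuming a between-group difference of 3.0 and a pooled SD of 6.0", and "With a two-sided alpha of 0.05 and power of 80"%, "this will require 63 participants to be randomised to each of the two interventions".

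No section names the baseline BACS composite or the continuous IQ score as a covariate.

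**The concern.** The article does state a covariate rule, so the objection is to the rule and not to missing detail. The rule assures only the stratification variables. Any other baseline value comes in through the clause on possible imbalance.

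In a randomised trial, an observed baseline imbalance is a chance event. It says little about whether a covariate is worth having, which depends on how well the covariate predicts the outcome. The baseline value of the same composite is probably the strongest predictor of the 6-month score, yet under this rule it could be left out because the arms happen to look alike. Two consequences follow:

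- The primary model is settled only after the data have been inspected.
- The trial may give up precision that measurements it already collects would supply.

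A smaller point is that IQ, if it enters as the two-class stratum, carries less information than the score from which the classes were made.

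**Working it through.** **1. The plan's own figure.** With a difference of 3.0, SD 6.0, two-sided alpha 0.05 and 80% power, the normal formula gives n per arm = 2 × (1.960 + 0.842)² / 0.50² = 62.8, so 63. The stated 63 reproduces. Power at 63 per arm is 80.1% by the normal approximation and 79.5% by the exact t-test. No covariate enters this calculation.

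**2. Inputs not in the documents (assumptions).**
- Correlation of IQ with 6-month BACS: r = 0.3 to 0.6. IQ is roughly normal, the relation is linear, and 100 lies near the middle of the sample.
- Correlation of baseline with 6-month BACS: p = 0.6 to 0.8. IQ is taken to correlate equally (r) with both BACS scores.
- The SD of 6.0 is the unadjusted SD at 6 months.
- 50 analysed per arm is an illustration of attrition; the article gives no rate.

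**3. Two-class against continuous IQ, no other covariate.** A split at the median of a normal variable keeps 2/π = 63.7% of the variance it explains. Residual variance, as a share of 6.0², is 1 − (2/π)r² for two classes and 1 − r² for the continuous score. Power uses the noncentral t with residual SD = 6.0 × √(residual variance) and 2n − 2 degrees of freedom, ignoring the one or two degrees of freedom spent on covariates.

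| r | Residual variance, two-class / continuous | Power, 63 per arm | Power, 50 per arm |
|---|---|---|---|
| 0.3 | 0.943 / 0.910 | 81.8% / 83.1% | 72.2% / 73.7% |
| 0.4 | 0.898 / 0.840 | 83.6% / 86.0% | 74.3% / 77.1% |
| 0.5 | 0.841 / 0.750 | 85.9% / 89.5% | 77.0% / 81.6% |
| 0.6 | 0.771 / 0.640 | 88.7% / 93.6% | 80.5% / 87.2% |

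With no covariate, power is 79.5% at 63 per arm and 69.7% at 50.

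A cut 0.5 SD from the mean keeps 58.1% rather than 63.7%, so under normality the loss of about 36% is close to the smallest possible.

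**4. With baseline BACS in the model.** The explained share is R² = (p² + c² − 2pc²) / (1 − c²), with c = r for continuous IQ and c = r√(2/π) for two classes. For example, with p = 0.7 and r = 0.5, continuous: (0.49 + 0.25 − 0.35) / 0.75 = 0.52, so residual variance is 0.48. The two-class value is 0.493.

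| p | r | Residual variance, two-class / continuous | Power, 63 per arm | Power, 50 per arm |
|---|---|---|---|---|
| 0.6 | 0.3 | 0.630 / 0.624 | 93.9% / 94.1% | 87.7% / 88.0% |
| 0.6 | 0.6 | 0.592 / 0.550 | 95.1% / 96.4% | 89.6% / 91.6% |
| 0.7 | 0.5 | 0.493 / 0.480 | 97.8% / 98.0% | 94.1% / 94.7% |
| 0.8 | 0.6 | 0.348 / 0.337 | 99.7% / 99.8% | 98.7% / 98.9% |

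**5. Where the gain comes from.** At r = 0.5 and 63 per arm, replacing the IQ classes by the score alone adds 89.5 − 85.9 = 3.6 points. Adding baseline BACS (p = 0.7) to the IQ classes adds 97.8 − 85.9 = 11.9 points, and the continuous score then adds only 98.0 − 97.8 = 0.2. Over the ranges tried, the largest further gain from continuous IQ is 96.4 − 95.1 = 1.3 points at 63 per arm and 91.6 − 89.6 = 2.0 at 50.

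**The case against.** **The two-class coding is inferred.** The *Statistical analyses* section gives no coding, and continuous IQ or baseline BACS could enter through the imbalance clause or be fixed in a SAP that is not shown. This stands in part: it cannot be said that IQ enters only as two classes. But the article states a rule, and on its plain reading nothing beyond the strata is assured.

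**Nothing is invalid, and the plan meets its own target.** Stratifying on IQ classes and adjusting for them is coherent, causes no bias and does not inflate the type I error. The sample size claims no benefit from covariates, so at 63 analysed per arm the two-class model already exceeds 80% in every scenario above. This stands. A reader might infer that the trial is underpowered because of its covariates; the documents do not support that. At an assumed 50 per arm, the shortfall comes from attrition, and two-class IQ still raises power from 69.7% to 72.2–80.5%.

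**Baseline BACS may be used elsewhere.** The secondary mixed model may use the baseline measurement, and the primary analysis is to be done by a blinded, independent statistician. Both soften the point. Neither fixes which covariates the primary model contains, and blinding does not make that choice independent of the data.

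**The size rests on assumed correlations.** This stands, and is why ranges are shown. At r = 0.3 without baseline BACS, the IQ coding is worth only 1.3 points of power.

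**Conclusion.** The point holds as an optional improvement. The stated rule leaves the probable best predictor of the primary outcome to be included or not according to observed imbalance. That makes the primary model data-dependent and gives up precision.

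Under the assumptions listed, power at 63 per arm is about 82–89% with two-class IQ alone, 83–94% with continuous IQ alone, and 94% to over 99% with baseline BACS included. At an assumed 50 analysed per arm, the figures are about 72–81%, 74–87% and 88–99%.

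A reader might infer that splitting IQ at 100 is the main fault, because it discards about a third of what IQ explains. The fraction is right under normality, but it is a share of IQ's contribution only. Once baseline BACS is in the model, continuous IQ adds at most about 1 to 2 points of power. Nor do the documents support a reading of bias or of failure to reach 80% at the planned size.

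**What to change.** State in the analysis section (or confirm in the SAP, before the data are analysed) that the 6-month model always includes the baseline value of the outcome, antipsychotic use as a factor, and IQ as the continuous baseline score in place of the two-class term, whatever balance is observed. Name the test that supplies the IQ score. Keep the IQ classes for randomisation.

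The priority is the baseline value of the outcome; continuous IQ is a minor addition. The cost is one sentence. No new data are needed, because both measures are collected before randomisation. Baseline BACS costs one degree of freedom, and replacing the IQ classes by the score costs none.
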